### Statistical considerations

This will be a superiority study undertaken to test the hypothesis that NHD leads to less LV mass progression compared to CvHD. Based upon observational data obtained by echocardiography (11), the baseline LV mass for both groups will be 147 +/- 8 g. To give the study the power (1-beta = 0.95) to detect a significant (alpha = 0.05, two-tailed test) 10 g difference in LV mass (a clinically important and statistically detectable difference given the use of CMR) between the 2 treatment groups, 32 patients are needed to complete the study. Assuming 20% dropout (due to transplantation or death over six months), 19 patients in each arm of the study will be enrolled.

All analyses will be undertaken by a data analyst blinded to the subject treatment assignment. Summary statistics will be used to describe the baseline characteristics of both groups. For the primary endpoint of change in LV mass, the intention-to-treat (ITT) approach will be used, including all enrolled patients who have at least one cMR measurement. The analysis of the primary end-point will be based on the difference between the groups in the change of LV mass over the study period. For patients who drop-out of the study (death or renal transplant) before the final cMR examination, we will assume no change in the baseline cMR parameters for the primary ITT analyses. This very conservative approach will likely bias the final results towards the null hypothesis. A similar approach will be used for the secondary endpoints (Table 2). Exploratory secondary analyses will be performed using an observed cases approach.

**Table 2 T2:** Primary analyses for primary (LV mass) and secondary outcomes

Factor	First Measure	Final Measure	Primary Analysis*
LV mass	Baseline	6 month visit	Comparison of mean change in LV mass for NHD vs control subjects
Blood pressure	Baseline visit – average of 5 and 10 minute readings	6 month visit – average of 5 and 10 minute readings	Comparison of mean change in systolic BP for NHD vs control subjects
Quality of Life	Baseline	6 month visit	Difference in the 6 month and baseline EQ-5D index scores for NHD vs control group – intention to treat, last observation carried forward
Anemia	Mean Hct and Epo administered for two months preceding baseline visit	Mean Hct and Epo administered for the final two months of the study	Mean change in hct/epo ratio for NHD vs control subjects

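### The sample-size figures do not reconcile: 19 per arm with 20% dropout leaves about 30 completers, not the 32 the protocol requires (a minor arithmetic correction)

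*Protocol article*

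**What the plan says.** Everything is in one paragraph of the protocol article, Statistical considerations.

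- Variability: "the baseline LV mass for both groups will be 147 +/- 8 g". The source is observational echocardiography. The spread is not labelled as a standard deviation.
- Target: "10 g difference in LV mass" between the two groups.
- Error rates: "alpha = 0.05, two-tailed test", and "To give the study the power (1-beta = 0.95) to detect a significant" that difference.
- Requirement: "32 patients are needed to complete the study", that is 16 per arm.
- Enrolment: "Assuming 20% dropout (due to transplantation or death over six months), 19 patients in each arm of the study will be enrolled".

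The next paragraph of the same section sets the primary analysis. It compares change in LV mass between the groups by intention to treat, and patients who leave before the final scan are kept with their change set to zero. An analysis of observed cases is exploratory. The section names no formula or test for the sample-size calculation.

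**The concern.** The requirement is put in terms of patients who finish, so enrolment has to be large enough that 32 remain after the assumed loss. At 19 per arm it is not. This is the only sample-size justification in the article, and it concerns the primary endpoint. The Discussion section says the study will help in designing a larger trial. A reader who takes the paragraph at face value will believe that the plan yields 32 completers and a 5% type II error. On its own inputs it yields about 30 completers and a somewhat larger type II error.

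**Working it through.** **Inputs**, all from Statistical considerations: difference 10 g; spread 8 g, read here as the SD of the analysed outcome; two-sided alpha 0.05; power 0.95; equal arms; 32 completers; 20% dropout; 19 enrolled per arm.

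**1. The plan's own requirement.** The normal approximation is n per arm = 2 × (1.960 + 1.645)² × 8² / 10² = 16.6, or 33.3 in total. Rounded up, this is 17 per arm. The stated 16 per arm is close, so 8 g was evidently used as the SD in a calculation of this kind.

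**2. Dropout inflation.**
- Expected completers as planned: 38 × (1 − 0.20) = 30.4, or 15.2 per arm.
- Enrolment needed for 32 completers: 32 / 0.80 = 40, or 20 per arm.
- The shortcut that matches the printed figure: 16 × 1.20 = 19.2, taken as 19.
- Largest dropout at which 38 enrolled still leaves 32: 1 − 32/38 = 15.8%.

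This step does not depend on the SD, the test or the power formula.

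**3. Power among completers** (standardised difference 10/8 = 1.25):

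| Completers per arm | Normal approximation | Two-sample t-test (non-central t) |
|---|---|---|
| 15 | 92.8% | 91.0% |
| 15.2 | 93.1% | 91.4% |
| 16 | 94.2% | 92.8% |
| 17 | 95.4% | 94.2% |
| 18 | 96.3% | 95.4% |

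At about 15 per arm, power is roughly 91–93%, so type II error is roughly 7–9%. At the stated 16 per arm, power is 93–94%.

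**4. Power of the planned primary analysis.** Assume that 10 g is the effect among completers, that the SD of change is 8 g, that dropout is random at 20%, and that dropouts are set to zero. The expected difference shrinks to 0.8 × 10 = 8 g. The variance in an arm whose completers change by a mean of m is 0.8 × 64 + 0.8 × 0.2 × m² = 51.2 + 0.16m². With 19 per arm and the normal approximation:
- Control change 0, NHD −10 g: variances 51.2 and 67.2; SE = √(118.4/19) = 2.50; 8/2.50 = 3.20; power about 89%.
- Control change +5 g, NHD −5 g: both variances 55.2; SE = √(110.4/19) = 2.41; 8/2.41 = 3.32; power about 91%.
- Control change −5 g, NHD −15 g: variances 55.2 and 87.2; SE = √(142.4/19) = 2.74; 8/2.74 = 2.92; power about 83%.

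Simulation of the same analysis with a t-test agrees: about 89–91% for a control change of 0 to +5 g, and about 81–84% at −5 g. The control-arm change is an assumption, because the article gives none.

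**The case against.** **The primary analysis keeps the dropouts, so completers are beside the point.** It is true that completer power does not describe the planned primary test, and any corrected text has to say so. But the protocol chose completers as its requirement. Keeping dropouts at zero change does not restore the power either, because it dilutes the effect. The protocol itself says that this handling pulls the result towards the null.

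**The precision is illusory.** The 8 g describes baseline mass by echocardiography, while the endpoint is change by cardiac MR. If 8 g is the SD at each visit, it is also the SD of change only when the correlation between visits is 0.5. Over an assumed correlation of 0.3 to 0.7, the SD of change runs from 9.5 to 6.2 g and the requirement from 24 to 10 per arm. Against that range, 19 versus 20 is small. This stands, and it is why the power figures are conditional on the plan's own inputs. The completer count in step 2 is unaffected.

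**A reader might infer that the 95% claim is simply false at 32 completers, or that the type II error is 9%.** The document supports neither. It names no formula. The normal approximation gives 94.2% at 16 per arm, under one point short. Only the t-test gives 92.8%. The 9% figure is the upper end of 7–9%.

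**A reader might also infer that the trial is seriously underpowered.** Completer power stays above 90% by both formulas, and the Background section calls the study a pilot.

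**Conclusion.** The inflation step is wrong on the protocol's own figures. Nineteen per arm with 20% dropout leaves about 30 completers, against the 32 required, and the division gives 20 per arm. That the error came from multiplying by 1.2 is an inference from the match, since the article does not show the step.

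The consequence is small: two enrolled patients, and completer power of about 91–93% instead of 95%. Part of that gap, about one to two points, is already present at 32 completers and is at rounding level. These power figures rest on reading 8 g as the SD of the outcome. The 89–91% for the intention-to-treat analysis rests in addition on random dropout and an assumed control-arm change of 0 to +5 g. It would be lower if LV mass fell in the control arm.

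This is a minor arithmetic correction. It does not threaten the endpoint, the conduct or the validity of the trial.

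**What to change.** Restate the enrolment sentence in one of two ways.

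- **Keep 19 per arm:** about 15 completers per arm are expected after 20% dropout, giving about 91–93% power for a 10 g difference at an SD of 8 g, among completers.
- **Correct the inflation:** enrol 20 per arm for 16 completers per arm, giving about 93–94% power on the same inputs.

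In either case, name the formula used, so that a single power figure can be printed. Add one sentence saying that this is completer power and that the primary intention-to-treat analysis, with dropouts set to no change, has somewhat lower power: at 19 per arm, about 89–91% under an assumed control-arm change of 0 to +5 g.

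The first option costs no patients and changes no procedure; the printed power becomes a few points less favourable. The second costs two patients. Keeping 0.95 as a completer figure would need 17 or 18 completers per arm, which is 17/0.8 = 21.25 or 18/0.8 = 22.5, so 22 or 23 enrolled per arm. This point alone does not call for that.

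### The zero-change rule for dropouts in the primary analysis is conservative only under conditions that the protocol cannot guarantee, and the stated power was not worked out for it

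*Protocol article*

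**What the plan says.** All points are in the protocol article, section Statistical considerations, unless noted.

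- The primary ITT set is every enrolled patient with at least one cMR, and the endpoint is the between-group difference in change of LV mass. For patients who leave through death or renal transplant before the final scan, "we will assume no change in the baseline cMR parameters for the primary ITT analyses".
- The justification is: "This very conservative approach will likely bias the final results towards the null hypothesis".
- The trial is a superiority study to "test the hypothesis that NHD leads to less LV mass progression compared to CvHD".
- The only other treatment of dropouts is exploratory: "Exploratory secondary analyses will be performed using an observed cases approach".
- The sample size uses "alpha = 0.05, two-tailed test", power of 0.95 and a "10 g difference in LV mass (a clinically important and statistically detectable difference given the use of CMR"). The only spread given is "the baseline LV mass for both groups will be 147 +/- 8 g", from echocardiography. This leads to 32 completers, and to 19 enrolled per arm after a 20% dropout allowance.
- Methods/design says that staggered entry is meant to avoid unequal dropout between the groups.
- The Abstract and Discussion justify LV mass as a surrogate for, and independent predictor of, cardiac mortality.

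**The concern.** A zero is a neutral score only if LV mass would on average have stayed the same. The hypothesis is framed as less progression. If LV mass tends to rise over six months, a zero is a good score, and the arm that loses more patients collects more good scores. If LV mass tends to fall, the reverse holds. The rule can therefore bias the comparison either way, and the protocol offers it as the safe choice for the confirmatory result.

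Two further matters follow. A patient who dies is entered as having a stable ventricle, in a trial whose endpoint is justified by its link with cardiac death. And the sample size treats dropouts as lost, whereas the analysis keeps them as zeros. The effect that the analysis estimates is then not the 10 g for which the trial was sized.

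**Working it through.** **Inputs from the protocol.** Two-sided alpha 0.05, power 0.95, difference 10 g, SD 8 g, 16 completers and 19 enrolled per arm, 20% dropout.

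**Inputs assumed.** The protocol gives no mean change by arm, no dropout by arm and no SD of the six-month cMR change. The 8 g baseline figure is used as the SD of change, dropout is unrelated to outcome, and a range of means and dropout splits is shown.

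**1. The plan's own figure.** n per arm = 2 × (1.960 + 1.645)² × 8² / 10² = 16.6, so 17 (34 in total, against 32 stated). With 16 per arm, power is 0.942 by normal approximation and 0.928 by t-test. The stated figure is reproduced to within two patients. The enrolment of 19 matches 16 × 1.2 = 19.2.

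**2. What the rule estimates.** With dropout d and mean change μ in an arm, the imputed data have mean (1 − d)μ and variance (1 − d) × 64 + d(1 − d)μ². The expected difference, NHD minus CvHD, is

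(1 − d_N)μ_N − (1 − d_C)μ_C.

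- Equal dropout d: (1 − d)(μ_N − μ_C). At 20%, 0.8 × 10 g = 8 g, which is towards the null.
- No true effect, common change μ: (d_C − d_N)μ. This is zero only if dropout is equal or μ is zero.

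**3. Type I error with no true effect** (simulated t-test, 19 per arm, SD 8 g):

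| Change in both arms | Dropout NHD / CvHD | False difference | Two-sided error |
|---|---|---|---|
| +10 g | 20% / 20% | 0 | 5.0% |
| 0 g | 30% / 10% | 0 | 5% |
| +3 g | 30% / 10% | −0.6 g | about 6% |
| +5 g | 30% / 10% | −1.0 g | about 7% |
| +10 g | 30% / 10% | −2.0 g | about 12% |
| +5 g | 25% / 15% | −0.5 g | 5.5% |
| +10 g | 25% / 15% | −1.0 g | 6.7% |

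Negative differences favour NHD. At +10 g and 30%/10%, nearly all the error (about 11.7 points) is a false claim for NHD. Reversing the dropout rates reverses the sign.

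**4. Direction with a true 10 g benefit and 30%/10% dropout.**
- Means +10 (NHD) and +20 (CvHD): 0.7 × 10 − 0.9 × 20 = −11 g, away from the null.
- Means −10 and 0: 0.7 × (−10) − 0 = −7 g, towards the null.

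**5. Power with equal 20% dropout, 19 per arm, true difference 10 g** (simulated t-test):

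| Means NHD / CvHD | Zero-change rule |
|---|---|
| −5 / +5 | 0.91 |
| −10 / 0 | 0.89 |
| 0 / +10 | 0.89 |
| +2 / +12 | 0.86 |

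A complete-case t-test in the same setting, with 19 × 0.8 = 15.2 expected completers per arm, has power of about 0.91. Imputation thus costs about 0 to 5 points in these scenarios. The rest of the gap from 0.95 comes from the completer count and from using a t-test. Only under large growth in both arms (+10 / +20) does the rule cost much more: power is then 0.70.

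To restore 95% power under the rule, n per arm = (v_N + v_C) × 3.605² / 8². For −5/+5 this is (55.2 + 55.2) × 12.995 / 64 = 22.4; for −10/0 it is (67.2 + 51.2) × 12.995 / 64 = 24.0. That is about 23 to 25 per arm.

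**The case against.** The strongest defence is that the protocol claims only a likely bias to the null, and that in the benign case it is right: with similar dropout unrelated to outcome, the estimate shrinks and type I error is held. The shrinkage to 8 g is that same conservatism. Staggered entry is aimed at unequal dropout. The Background and Discussion report regression of LV mass on NHD, and if NHD regresses while control is stable, extra dropout on NHD works against NHD. Both arms are treated to a blood pressure goal, so gains of 10 g in both are not an obvious expectation. All of this stands, and it limits the size of the concern. It does not make the justification general: staggered entry aligns timing but cannot equalise deaths and transplants, and the hypothesis itself is written in terms of progression.

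Three stronger readings are tempting and are not supported.

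- *The rule is anti-conservative, or favours NHD.* It can do either. The direction depends on dropout by arm and mean change, and the protocol gives neither.
- *Imputation destroys the stated power.* Complete cases already give only about 0.91, so most of the gap has other causes.
- *About four patients will die and be scored as stable.* This comes from 38 × (1 − 0.8^0.5) = 4.0, using the Background's mortality of nearly 20% per year. That figure describes dialysis patients in general, not volunteers able to train for home NHD.

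It is also fair that a missing-at-random model has only baseline data from which to inform a missing month-6 scan, and that it implies an LV mass for patients who died.

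**Conclusion.** The point holds in a limited form. The claim that the primary rule is very conservative is true under equal, uninformative dropout and is not assured otherwise. With 30%/10% dropout and no true effect, type I error rises to about 6% for a common change of 3 g, 7% for 5 g and 12% for 10 g. With a milder 25%/15% split it is 5.5% at 5 g and 6.7% at 10 g. These figures rest on assumed dropout splits and mean changes and on 8 g as the SD of change.

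Separately, and without any such assumption, scoring a death as a stable ventricle fits poorly with the rationale for the endpoint. At the planned 20% dropout in each arm the stated analysis targets about 8 g, not the 10 g used for sizing. Power for that analysis is about 86–91% in the moderate scenarios.

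**What to change.** - Make the primary analysis a baseline-adjusted comparison of month-6 LV mass that is valid under missing-at-random: ANCOVA, or a constrained longitudinal model that uses every patient with at least one cMR.
- Keep the zero-change rule as a sensitivity analysis. Add a tipping-point analysis that varies the assumed change of dropouts separately by arm, and a separate analysis that treats deaths as unfavourable outcomes.
- Replace the claim of conservatism with the conditions under which the rule biases to the null: similar dropout in both arms, unrelated to outcome.
- Restate the power for the analysis chosen.

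The cost is a change of wording and some programming, to be settled before allocation is unblinded. No new data are needed. The downside is that the primary result then rests on a missing-at-random assumption, with only baseline data to inform the missing month-6 scans. The tipping-point and death analyses are there to test how much that matters.

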## Methods/design

This study will be a prospective, two-center, parallel-group randomized, controlled study, with blinding of outcome assessors and data analysts. Approval has been granted by the local bioethics committees at the University of Calgary and the University of Alberta.

Eligible patients are men or women greater than 18 years of age who are currently receiving any hemodialysis modality (in-center, self-care or home) excluding current NHD. To be enrolled in this study, patients must be interested in and willing to train for NHD. Exclusion criteria include the inability to perform NHD due to physical or mental incapacity or the inability to provide informed consent.

Those patients meeting the inclusion and exclusion criteria will be randomized to either the NHD or control group. Randomization will be performed using a computer generated sequence in blocks of four patients. Randomization will be stratified by center and by baseline dialytic modality (self-care/home hemodialysis vs. in-center hemodialysis). Concealment will be assured through the use of sealed, opaque envelopes. Given the logistics of training patients within a nocturnal dialysis program, randomization will occur at one time point for patients willing to enter the study; however, patient entry into the study (i.e. the baseline study visit) will be staggered over time to facilitate NHD training in an orderly fashion. This will create a similar number of intervention and control patients at any given time point. This approach will be used to avoid an imbalance in drop-out rates between the two groups. Subjects randomized to CvHD will be eligible to commence NHD after study exit (six months).

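### The primary analysis is stated as a comparison of mean change that uses neither baseline LV mass as a covariate nor the stratification factors; it is valid, but may give up precision that ANCOVA would recover at almost no cost

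*Protocol article*

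**What the plan says.** The Statistical considerations section describes the primary analysis twice. The text states: "The analysis of the primary end-point will be based on the difference between the groups in the change of LV mass over the study period". The LV mass row of Table 2 reads "Comparison of mean change in LV mass for NHD vs control subjects". The rows for systolic blood pressure, EQ-5D, anemia and mineral metabolism have the same form, a between-group comparison of change. No row names a covariate, a model or a test.

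The Methods/design section says of allocation: "Randomization will be stratified by center and by baseline dialytic modality (self-care/home hemodialysis vs. in-center hemodialysis"), and "Randomization will be performed using a computer generated sequence in blocks of four patients". Two centers and two modality groups give four strata. Neither factor appears again in the analysis. Baseline LV mass is measured in both arms (Table 1), but in the stated analysis it enters only by subtraction.

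**The concern.** A change score fixes the coefficient on the baseline value at one. When the correlation between the two visits is below one, the best coefficient is smaller. The change score then carries avoidable noise, and a chance baseline difference between small arms feeds into the estimate through regression to the mean. With 19 patients per arm enrolled and 16 per arm needed to complete, such differences are to be expected.

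Stratified randomization has a separate consequence. If center or modality predicts change in LV mass, balancing on them reduces the true variability of the treatment estimate. An analysis that leaves them out does not credit that reduction and reports a standard error that is too large. What is at stake is power and interval width in a very small trial, not the validity of a positive result.

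**Working it through.** **Inputs from the article (Statistical considerations, Methods/design).** Baseline: "the baseline LV mass for both groups will be 147 +/- 8 g", with the 8 g taken as an SD. Difference 10 g, power 0.95, two-sided alpha 0.05. Completers: "32 patients are needed to complete the study", that is 16 per arm. Enrolment 19 per arm. Four strata, blocks of four, taken as 1:1.

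**Assumed, because the article does not give them.** The baseline-to-6-month correlation r, and the share of the variance of change that the strata explain. Both are shown as ranges. Equal variance at the two visits and complete data are also assumed.

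**1. The plan's own figure.** n per arm = 2(1.960 + 1.645)² × 8²/10² = 16.63, so 17 per arm or 34 in total, within two patients of 32. Power at 16 per arm is 94.2% (normal) or 92.8% (t-test). The stated number therefore agrees with a plain two-sample formula with no covariate term.

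**2. Baseline adjustment, large samples.** With SD s at each visit:
- Var(change) = 2s²(1 − r)
- residual variance under ANCOVA = s²(1 − r²)
- ratio = (1 + r)/2

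This gives 0.75 at r = 0.5, 0.85 at 0.7, 0.90 at 0.8 and 0.95 at 0.9.

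**3. Baseline adjustment at this sample size.** The formula in step 2 ignores the cost of estimating coefficients. The model with baseline, center and modality was simulated at N = 32, with permuted blocks of four within strata and strata unrelated to outcome:

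| r | large-sample ratio | actual ratio at N = 32 |
|---|---|---|
| 0.5 | 0.75 | about 0.79 |
| 0.7 | 0.85 | about 0.89 |
| 0.8 | 0.90 | about 0.94 |
| 0.9 | 0.95 | about 0.99 |
| 0.95 | 0.975 | about 1.03 |

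The gain is about 20% at r = 0.5 and 6% at 0.8. It is essentially nil at 0.9, with a slight loss at 0.95.

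In power terms, take N = 30 and a true effect of 0.9 SD of change. Plain comparison against ANCOVA: 66.1% and 75.7% at r = 0.5; 65.7% and 68.4% at 0.8; 66.6% and 65.4% at 0.95.

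**4. Chance imbalance.** At SD 8 g and 16 per arm, the SE of the baseline difference is 8√(2/16) = 2.8 g. An imbalance of one SE shifts the expected change-score difference by (1 − r) × 2.8 g: 1.4 g at r = 0.5 and 0.6 g at r = 0.8, against a 10 g target. This shift is conditional on the observed imbalance and averages to zero over randomization.

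**5. Strata left out of the analysis.** Simulation with N = 38, four strata, blocks of four and a total SD of change of 8 g (size from 8,000 runs; power at a 7 g effect from 4,000 runs):

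| variance explained by strata | reported SE, plain | true SE, plain | size, plain | size, adjusted | power, plain | power, adjusted |
|---|---|---|---|---|---|---|
| 0% | 2.57 | 2.58 | 4.7% | 4.6% | 74% | 74% |
| 10% | 2.59 | 2.47 | 4.0% | 4.8% | 76% | 79% |
| 30% | 2.59 | 2.22 | 2.2% | 4.9% | 78% | 88% |
| 50% | 2.60 | 1.91 | 0.9% | 4.6% | not run | not run |

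The reported SE is too large by a factor of 2.59/2.47 = 1.05 at 10% and 2.59/2.22 = 1.17 at 30%. With non-prognostic strata it is correct.

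**The case against.** The strongest objection is that the article never says the comparison is unadjusted. It names a contrast. An ANCOVA of change with stratum terms also compares mean change, and covariates are often left to an analysis plan that is not shown. This stands as a limit on wording: the plain reading is an inference. It does not dispose of the point. Table 2 is presented as the primary analyses, the text repeats the same form, and the section is specific about the analysis set, the no-change assumption for dropouts and the observed-case analyses. A stated method can be replaced by a better one.

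Three stronger readings are tempting, and the documents support none of them.

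- **The analysis is biased or its error rate inflated.** Over randomization the change-score estimate is unbiased. Leaving out the strata makes intervals too wide, never too narrow, and only if the strata are prognostic. The article gives no evidence that they are.
- **ANCOVA can never do worse.** That holds in large samples. At about 32 patients it fails for very high r, as step 3 shows. The abstract stresses the high reproducibility of cMR, which makes a high r plausible.
- **A large power gain can be quoted.** That needs an SD of change the article does not give. For example, 12 g is incompatible with 8 g per visit at any positive correlation: 144 = 2 × 64 × (1 − r) gives r = −0.125. With 8 g per visit and 15 per arm, the plain change score already has 91% power for 10 g at r = 0.5 and 99% at 0.7.

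**Conclusion.** The point holds as one of efficiency. The stated primary analysis, read as a plain change-score comparison, is valid but leaves out information the trial collects and a design feature it uses. The variance to be recovered is about 20% at r = 0.5, 6% at r = 0.8 and close to none at 0.9 or above. In addition, the plain test is conservative if center and modality predict change, with size about 4% if they explain 10% of the variance and about 2% at 30%. The correlation and the prognostic strength of the strata are assumptions, so the actual gain may lie anywhere from negligible to worthwhile. The change is worth making because the sample is small, the cost is slight, and naming the covariates in advance removes a later choice between adjusted and unadjusted results.

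**What to change.** In Table 2 and the accompanying text, state that change in LV mass (or, equivalently for the treatment effect, 6-month LV mass) is compared between arms by ANCOVA with treatment, baseline LV mass, center and baseline dialysis modality, reported as an estimate with a 95% CI. Use the same form for systolic blood pressure, EQ-5D, the anemia ratio and the calcium-phosphate product, each with its own baseline value and the two stratification factors. Keep the raw comparison of mean change as a supportive analysis.

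The cost is a wording change. Baseline values are already collected and both factors are known at randomization. Three degrees of freedom are spent, with a negligible loss of precision if the correlation is very high and the strata are not prognostic.
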